### Participant recruitment

The target study population includes children aged 5–17 years and adults aged 18 years and older with asthma from 80 households. Initially, approximately 88 households will be recruited to account for potential dropout and ensure that the required sample size is maintained throughout the study period. Participants will be primarily recruited from applicants to Rebuilding Together North Texas (RTNTX), a nonprofit organization that administers the Safe & Healthy Homes program. This program provides essential home repairs, safety improvements, and accessibility modifications for low-income residents across diverse communities in the DFW area.

Eligibility requirements for participation in the study include: (1) homes must have at least one occupant with self-reported physician-diagnosed asthma; (2) homes must be non-smoking; (3) homes must be owner-occupied; and (4) participants must agree to participate in the entire 2-year study duration and allow for five home visits by the research team. Potentially eligible participants will complete an electronic screening form prior to enrollment, based on the inclusion and exclusion criteria listed below.

The inclusion criteria:

Age: children 5–17 years; adults ≥18 years.Individuals with physician-diagnosed asthma.Residency in the DFW area.English speaking and writing.Able to provide consent.Able to communicate regularly by phone.

The exclusion criteria:

Homes with any current smokersAnticipated relocation outside the DFW area within the two-year study period.Hazardous conditions and/or safety concerns in or around the participant’s home.Use of any device not provided as part of the study, including ERVs or portable HEPA air cleaners, in the participant’s home at any time during the trial.

Participant engagement will be maintained through home visits and monthly asthma surveys via phone. Primary participants will receive a total of $200 in gift cards across the four follow-up visits (V1-V4), and additional eligible family members may receive $100 each. Participants will have the option to keep the intervention device; those assigned to a sham device will receive an active device at study completion. Participants who do not complete required assessments will not be randomized or remain in the study. Compensation is contingent upon completing all study procedures, and participants who withdraw or fail to complete visits will forfeit subsequent payments.

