### Data management and statistical analysis plan

The full data collection will include three categories of data: (1) human subject data, including demographic and socioeconomic characteristics and asthma-related health outcomes collected via baseline and follow-up questionnaires; (2) housing characteristics, including building and dwelling information; and (3) environmental exposure data, including indoor and outdoor air quality and mold measurements. All data will be de-identified prior to analysis to protect participant confidentiality, with direct identifiers removed before sharing. Data will be stored as comma-separated text files and spreadsheet files on a secure central server in the PI’s laboratory and processed electronically using Stata or Python in appropriate analysis formats. De-identified data will be shared only with the PI. Missing data will be handled using multiple imputation under the missing-at-random assumption, where collected data will be used to predict missing values. At least 20 imputed datasets will be generated, and convergence diagnostics and comparisons between observed and imputed data will be performed to assess plausibility [51]. Mixed-effects models for repeated measures will be used to account for within-subject correlations, and sensitivity analyses will compare complete-case and multiple imputation results.

Descriptive statistics will summarize participant demographics (e.g., age, sex, race/ethnicity, household income) and study variables by group, with continuous variables presented as means, medians, standard deviations, interquartile ranges (IQRs), or other distributional parameters, and categorical variables as frequencies and percentages. Appropriate statistical tests will be applied based on data type and distribution, including paired and unpaired t-tests, Wilcoxon signed-rank or rank-sum tests, and chi-square tests for categorical comparisons.

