The primary analyses will follow the intention-to-treat (ITT) principle, including all randomized households analyzed according to their assigned intervention group, to evaluate the effects of ERVs and portable HEPA air cleaners on IAQ, mold reduction, and asthma-related health outcomes by comparing the intervention and control (sham) groups using repeated measures analysis of variance (ANOVA) with a within-between interaction. Pairwise comparisons will be conducted between each intervention and control group (Group 1 vs. Group 2, Group 3 vs. Group 4) and between intervention groups (Group 1 vs. Group 3), using Tukey’s Honest Significant Difference (HSD) test to adjust for multiple comparisons. Repeated monthly ACT scores will be analyzed using multivariate mixed-effects models to account for within-subject correlations over time. Per-protocol (PP) analyses will be conducted as sensitivity analyses and will include only households that adequately adhered to the assigned intervention protocol. Intervention adherence will be assessed using plug load logger data for both ERV and air cleaner units, including device operation status and operating duration [52]. Additionally, subgroup analyses will be conducted to explore whether intervention effects differ by demographic and socioeconomic characteristics, baseline asthma severity, and baseline IAQ.

For secondary analyses, multivariate linear and logistic regression models will examine associations among housing characteristics, occupant behaviors, indoor environmental exposures (e.g., air pollutants and mold), and asthma-related health outcomes. Housing characteristics will be considered as potential covariates or confounders, when applicable, based on biological plausibility and statistical considerations. Prior to multivariable modeling, correlations among environmental exposure variables (e.g., PM, NO_2_, VOCs, and mold indices) will be evaluated using Pearson or Spearman correlation coefficients, depending on data distribution. Variance inflation factors (VIFs) will also be calculated to assess multicollinearity among predictors. Highly correlated exposures will not be included simultaneously in the same model to minimize multicollinearity, overfitting, and unstable estimates.

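### The rule that non-completers do not remain in the study is not limited to the period before randomisation, so it creates avoidable missing data and sits badly with the ITT analysis of all randomised households

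*Protocol article*

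**What the plan says.** Four statements in the protocol article bear on this point.

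- **Retention (Participant recruitment).** "Participants who do not complete required assessments will not be randomized or remain in the study". The next sentence deals with money only: "participants who withdraw or fail to complete visits will forfeit subsequent payments".
- **Device exclusion (same section, exclusion list).** "Use of any device not provided as part of the study, including ERVs or portable HEPA air cleaners", followed by "in the participant’s home at any time during the trial". The section says that these criteria are applied through an electronic screening form before enrolment.
- **Analysis population (Data management and statistical analysis plan).** The primary analysis is ITT, "including all randomized households analyzed according to their assigned intervention group", using "repeated measures analysis of variance (ANOVA) with a within-between interaction"; monthly ACT scores are to be analysed with mixed-effects models. Households that did not adhere adequately are left out only in a per-protocol sensitivity analysis.
- **Missing data (same section).** "Missing data will be handled using multiple imputation under the missing-at-random assumption", and "sensitivity analyses will compare complete-case and multiple imputation results".

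The Study design section places two follow-up visits before the intervention and two after it. The Power calculations section counts 24 monthly ACT surveys and allows for 10% dropout.

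**The concern.** The retention rule uses one sentence for two different situations. Declining to randomise someone who has not completed the run-in harms nothing, because no comparison between arms exists yet. Ending the participation of someone already randomised is different. Missing a survey or visit can depend on how well the asthma is controlled, and that is what the devices are meant to change.

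The rest of the plan assumes that incomplete participants stay. Imputation assumes that missed assessments are tolerated, and a per-protocol subset assumes that non-adherent homes are still in the trial. The retention rule says that a missed assessment ends participation. An isolated gap could then become the loss of everything that follows, by the trial's own choice.

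The person applying the rule may also know the assignment: the trial is single-blind, the principal investigators hold the randomisation sequence and oversee the study, and there is no data monitoring committee. An analysis plan written later cannot recover outcomes that were never collected.

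**Working it through.** **1. Does the rule reach randomised participants?** Randomisation follows the pre-intervention period. V3, V4 and about 12 of the 24 monthly ACT surveys therefore come after it. The words about remaining in the study carry no time limit, so on their plain reading the answer is yes.

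**2. What one removal costs.** In the strictest reading, a participant who misses the third post-intervention survey and is then removed loses 12 − 3 = 9 further monthly surveys, plus any visit still to come. One missing value becomes ten.

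**3. How a removed household enters the ITT analysis.** A conventional repeated measures ANOVA needs the full series, so later values would have to be imputed. Imputation under missing-at-random can use pre-intervention scores and any earlier post-intervention scores, and may recover part of the loss. The planned comparison with complete cases does not test the missing-at-random assumption, because complete-case results are at least as exposed to the same selection.

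**4. The plan's own figure, and the margin for losses.** For the within-between interaction:

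- λ = f²·N·m/(1 − ρ), df1 = (k − 1)(m − 1), df2 = (N − k)(m − 1)
- From Table 1: f = 0.10, m = 24, k = 4, α = 0.05. Assumed, because not stated: ρ = 0.5 and sphericity.
- N = 76: λ = 0.01 × 76 × 24/0.5 = 36.48, df 69 and 1656, power 0.815. Table 1 gives 0.82, so the figure reproduces.

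| Households with full data | Power |
|---|---|
| 88 | 0.89 |
| 80 | 0.84 |
| 76 | 0.82 |
| 75 | 0.81 |
| 74 | 0.7998 |
| 72 | 0.78 |
| 68 | 0.75 |
| 60 | 0.67 |

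Under these assumptions, losing 14 of 88 households (16%) takes small-effect power just below 0.80. Removals use up that margin.

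**5. Bias illustration A: sham-only removal, removed data discarded.** Assume 20 homes per arm. The shift in the sham mean is (homes removed × deviation)/20.

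- 3 homes, 0.8 SD worse than the others: 3 × 0.8/20 = 0.12 SD
- 2 homes, 1.0 SD worse: 2 × 1.0/20 = 0.10 SD

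For scale, if both active arms shift by δ at the midpoint and the sham arms do not, each interaction term is ±δ/4, so f = δ/4. Then f = 0.10 means δ = 0.40 SD, and the shifts are 0.10/0.40 = 25% and 0.12/0.40 = 30% of it.

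**6. Bias illustration B: removal in both arms, true effect zero, retained participants only.** Assume an ACT SD of 4 points, a correlation r of 0.3 to 0.5 between outcome and tendency to be removed, and poorer control making removal more likely. With proportion p removed, the retained mean rises by r × SD × φ(z)/(1 − p), where z is the normal quantile of p. The factor φ(z)/(1 − p) is 0.109 at 5%, 0.274 at 15% and 0.424 at 25%.

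| Removed, active vs sham | Bias in ACT points (r = 0.3; r = 0.5) | In SD |
|---|---|---|
| 10% vs 10% | 0; 0 | 0 |
| 5% vs 15% | 1.2 × (0.109 − 0.274) = −0.20; 2.0 × (0.109 − 0.274) = −0.33 | 0.05 to 0.08 |
| 5% vs 25% | 1.2 × (0.109 − 0.424) = −0.38; 2.0 × (0.109 − 0.424) = −0.63 | 0.09 to 0.16 |

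The sign follows from the assumed mechanism. More removal in the active arms would reverse it.

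**The case against.** The strongest reply is that the retention rule governs participation, while the analysis section governs who is analysed and says that every randomised household is included. Nothing states that a non-completer leaves the ITT set. With imputation, mixed models and a 10% dropout allowance, a household whose follow-up ends can still be analysed as randomised. This stands. A reader might infer that ITT cannot be carried out, or that post-randomisation behaviour selects the primary sample; the text supports neither. It supports something narrower: ITT would rest partly on imputed outcomes that the trial chose not to collect.

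A reader might also infer that randomised homes which later acquire their own device are removed. That criterion is applied on a pre-enrolment screening form, beside another forward-looking condition about anticipated relocation, and the per-protocol analysis already provides for inadequate adherence. Removal is therefore only a possible reading of loose wording.

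Two further points stand. The rule concerns participants while the ITT unit is the household, so in homes with several participants losing one is not losing the home. And participants are blinded, so unequal removal cannot be presumed; with equal removal in illustration B the bias is zero.

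The reply does not explain why a randomised participant's follow-up should stop at all. That is a stated rule, not detail left to a fuller document.

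**Conclusion.** The concern holds in a limited form. As written, the non-completion rule applies after randomisation and ends outcome collection because of post-randomisation behaviour. The missing data it creates are avoidable and possibly informative. It fits poorly with the imputation plan and with ITT of all randomised households. The device exclusion needs clearer wording but is not shown to be a removal rule.

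Neither the size nor the direction of any bias can be established from the document. The 0.10 to 0.12 SD figures assume 20 homes per arm, removal in sham only, chosen deviations, and none of the removed homes' data used. Illustration B runs from zero to 0.16 SD, also on assumed inputs and retained data only. No planned figure is wrong, and the stated analysis population is right. This should be fixed, but it does not invalidate the design.

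**What to change.** - Limit the non-completion rule to the period before randomisation.
- State that the non-study device exclusion is applied at screening.
- State that, after randomisation, neither a missed assessment nor use of a non-study device ends ACT, visit or sensor data collection, where the participant still consents and collection is feasible. This leaves room for relocation or a hazard in the home.
- State that the household stays in the ITT set, and that non-study device use is recorded and handled in the per-protocol sensitivity analysis already planned.

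These changes concern data collection and analysis only. The forfeiture of payments can stay as it is.

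The cost is a few sentences in the recruitment section, the consent text if it repeats them, and some effort to follow less compliant homes. No visits are added. The article reports that recruitment is under way but data collection has not started, so the change is cheapest now.

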### Interventions

The AIRVAC study will involve ERV and HEPA air cleaner interventions aimed at improving IAQ and asthma-related health outcomes. Following the pre-intervention period, participants will be randomized to receive one of four interventions during the 1-year post-intervention period: (1) active ERV, (2) sham (placebo) ERV, (3) active portable HEPA air cleaner, or (4) sham (placebo) portable HEPA air cleaner.

Due to the specific housing conditions required for ERV installation, including accessible ductwork for supply and exhaust, adequate space and access for the ERV unit, electrical safety, and proper sealing of penetrations, a constrained randomization approach will be employed. Prior to randomization, each home will undergo an ERV installation feasibility assessment based on the information collected during the initial walk-through visit (V0). Homes that meet the ERV installation criteria will be eligible for assignment to ERV or portable air cleaner study arms, whereas homes that do not meet the ERV installation criteria will only be eligible for portable air cleaner study arms.

After intervention eligibility is determined, participants will be randomly assigned to the available active or sham groups using a computer-generated randomization sequence in Stata (v.19) [35]. Stratified randomization will be used to maintain balance across the four study arms within predefined strata based on key housing and participant characteristics. Housing characteristics will include building envelope air leakage measured by blower door testing, home size, and exhaust fans, while participant characteristics will include baseline health status. The randomization sequence will be generated and securely maintained by the PIs. Allocation assignments will remain concealed until completion of eligibility confirmation and baseline assessments. All participants will remain blinded to whether they receive the active or sham intervention throughout the entire study duration. To maintain participant blinding, all field research staff and HVAC contractors will be trained not to disclose intervention assignments to participants.

For the 40 homes assigned to the ERV intervention, we will install a Broan-NuTone B160E75RS/T units. The required airflow rate of each unit will be determined based on the floor area and number of bedrooms, in accordance with ASHRAE Standard 62.2–2025, *Ventilation and Acceptable Indoor Air Quality in Residential Buildings* [36]. The building envelope leakage measured during the initial home assessments will be applied as infiltration credits in the ventilation rate calculations to account for natural air leakage. The ERV units will then operate continuously at the specified ventilation rate throughout the intervention period.

Sham ERVs will be installed in the same manner as active units but will be programmed to operate in recirculation mode, without supplying outdoor air or altering ventilation rates. They will draw indoor air from the home and return it without any dilution or exchange with outdoor air, as the outdoor air intake damper remains closed. Participants will not have access to the control panel settings during the study period. This modification will maintain participant blinding, as occupants will experience airflows and fan noise similar to those of active ERVs.

Forty (40) homes in the air cleaner group will receive a Medify Air MA-112 unit, primarily placed in the living room (or in the bedroom if occupants spend the majority of their time). In cases where additional eligible family members reside in the same household, an additional Medify Air MA-50 unit will be deployed in their bedrooms. Both air cleaners are equipped with HEPA and activated carbon filters. In homes assigned to the sham control group, filters will be removed from the air cleaner units. Both active and sham air cleaner units will be sealed and have identical external appearance and installation configurations to maintain participant blinding.

During scheduled home visits in the post-intervention period, field staff will check the ERV and air cleaner units to verify proper operation and confirm that blinding measures are maintained, including ensuring that ERV control panel settings remain unchanged and inaccessible to participants and that air cleaner unit seals remain intact.

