### Power calculations

The sample size and statistical power for this 4-arm parallel-group randomized controlled trial is analyzed for various scenarios based on a range of likely magnitudes of outcomes for asthma-related health outcome and environmental exposure assessments (Table 1). Calculations are made utilizing a robust statistical software tool, G*Power ver. 3.1.9.7, for a repeated measures ANOVA with a within-between interaction [49]. A range of effect sizes from small (Cohen’s f = 0.10), medium (f = 0.25), to large (f = 0.40) are considered to accommodate varying expected intervention effects, ensuring both robustness and generalizability of the findings [50]. Sample size calculations were conducted for the health outcomes (ACT and PFT) and environmental outcomes (IAQ and mold measurements). Required sample sizes were estimated based on expected effect sizes to achieve a statistical power >0.80 and adjusted for a 10% dropout rate. For monthly ACT surveys (n = 24) and monthly average low-cost IAQ measurements (n = 24), the required sample sizes ranged from 84 households for a small effect size (0.10) to 9 households for a large effect size (0.40). For PFT and mold measurements, the required sample sizes were estimated at 220 and 308 households, respectively, for detecting a small effect size (0.10); 40 and 53 households, respectively, for a medium effect size (0.25); and 18 and 26 households, respectively, for a large effect size (0.40). Although larger sample sizes were required to detect a small effect size (0.1) for PFT and mold, these estimates represent the sample sizes needed to detect very small changes. Further, the AIRVAC study was primarily designed to evaluate intervention effects on asthma outcomes and IAQ, for which the estimated sample sizes were within the planned recruitment range. Therefore, the final target sample size was set at 80 households, with an initial recruitment target of 88 households to account for potential dropout.

**Table 1 pone.0358221.t001:** Sample size calculations.

Effect Size (Cohen’s f for ANOVA)	Small			Medium			Large
	0.1	0.15	0.2	0.25	0.3	0.35	0.4

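### The trial randomises by four factors and by ERV feasibility, but the stated primary model names none of them, and four-arm balance within strata cannot apply to homes that cannot take an ERV

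*Protocol article*

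**What the plan says.** **Allocation (protocol article, Interventions).** Each home is first assessed for whether an ERV can be installed, and "homes that do not meet the ERV installation criteria will only be eligible for portable air cleaner study arms". Homes are then assigned at random among the arms open to them. The stated aim is: "Stratified randomization will be used to maintain balance across the four study arms within predefined strata based on key housing and participant characteristics". On the housing factors the section says: "Housing characteristics will include building envelope air leakage measured by blower door testing, home size, and exhaust fans". The one participant factor named is health status at baseline. The section gives no cut-points, number of levels or block size. It also fixes the device split, with 40 air cleaner homes and an ERV count given as: "For the 40 homes assigned to the ERV intervention".

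**Size (Power calculations).** "the final target sample size was set at 80 households, with an initial recruitment target of 88 households to account for potential dropout".

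**Analysis (Data management and statistical analysis plan).** The primary intention-to-treat test is a repeated measures ANOVA with a within-between interaction. The pairwise comparisons are Group 1 vs 2, Group 3 vs 4 and Group 1 vs 3. Monthly ACT scores go into mixed-effects models with no covariates listed. Housing factors are mentioned once, in the paragraph on secondary analyses: "Housing characteristics will be considered as potential covariates or confounders, when applicable". ERV feasibility does not appear in the analysis text.

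**The concern.** Three things do not fit together.

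1. Four stratification factors plus a feasibility layer are a lot for 80 homes and four arms, so cells may be too small for blocks to fill.
2. The promise of balance over all four arms within strata conflicts with the rule, in the same section, that some homes can reach only two arms.
3. The primary model as stated does not use the variables by which homes are allocated.

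Two things are at stake. One is precision, which stratification provides but an analysis without the factors does not report. The other is the device comparison, Group 1 vs Group 3, where feasibility differs between the groups by design and not by chance. Feasibility depends on ductwork, space, electrical safety and sealing, so infeasible homes may also differ in how they respond to a device or change over time.

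**Working it through.** **Inputs.** From the documents: N = 80 homes (88 recruited), four arms, 40 ERV and 40 air cleaner homes, at least four stratification factors, and two feasibility levels. Assumed because not stated: all factors binary with equal frequencies, full crossing, permuted blocks, and equal active:sham allocation (20 per arm). The feasible share q is not stated, but 40 ERV homes out of 80 require q of at least 0.5.

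**1. The plan's own figures.** The article gives no number of strata. Its sample size reproduces. For ACT/IAQ with f = 0.10, N = 76 and m = 24, assuming correlation 0.5 and full sphericity, lambda = 0.01 × 76 × 24 / 0.5 = 36.48, df1 = 3 × 23 = 69 and df2 = 72 × 23 = 1656. Power is 0.815 against the stated 0.82. Further, 76 × 1.1 = 83.6, rounded up to 84, and 80 × 1.1 = 88.

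**2. Homes per cell.**
- Four binary factors: 2^4 = 16 strata; 80/16 = 5.0 (88/16 = 5.5). This exceeds four arms.
- Crossed with feasibility: 32 cells; 80/32 = 2.5 (88/32 = 2.75).
- One factor with three levels, before feasibility: 24 strata; 80/24 = 3.3.

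By layer, feasible cells hold 5q homes for four arms and infeasible cells hold 5(1 − q) homes for two arms. For every q from 0.5 to below 1, at least one layer has fewer homes per cell than arms. At N = 80 both do when q lies between 0.6 and 0.8.

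**3. Incomplete blocks.** With blocks of four throughout, 30% of homes sit in incomplete blocks at 16 strata and 61% at 32 cells. With blocks of two for infeasible homes, the 32-cell figure is 37-40% for q from 0.5 to 0.9.

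**4. Covariate balance.** The root-mean-square difference in a binary factor's prevalence between two arms is 0.16 without stratification, 0.07 with 16 strata, 0.10 with 32 cells (all treated as four-arm) and 0.13 with 81 strata. Balance weakens as cells multiply but stays better than with no stratification. The mean gap between the largest and smallest arm is 3.7 homes at 16 strata and 5.4 at 32.

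**5. Standard errors.** Simulation: one outcome per home with variance 1, a share R² explained by the factors, stratified blocks of four, N = 80. Without stratification the contrast has SD √(2/20) = 0.316.

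| Cells | R² | True SD, unadjusted | Reported SE, unadjusted | Ratio | Reported SE, adjusted |
|---|---|---|---|---|---|
| 16 | 0.10 | 0.303 | 0.317 | 1.05 | 0.302 |
| 16 | 0.40 | 0.264 | 0.320 | 1.21 | 0.247 |
| 32 | 0.10 | 0.309 | 0.318 | 1.03 | 0.305 |
| 32 | 0.40 | 0.278 | 0.320 | 1.15 | 0.249 |

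The unadjusted SE is therefore 5-21% too large with 16 strata, and 3-15% with 32 cells treated as four-arm. For a group-by-time test, the outcome should be read as each home's pre-to-post change, because stable differences between homes cancel. R² is then the share of variance in change.

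**6. Group 1 vs Group 3.** All 80(1 − q) infeasible homes must be among the 40 air cleaner homes, and none can be among the ERV homes.

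| q | Infeasible homes | Share of air cleaner homes | ERV homes if feasible homes are split 1:1:1:1 (40q) |
|---|---|---|---|
| 0.9 | 8 | 8/40 = 20% | 36 |
| 0.8 | 16 | 16/40 = 40% | 32 |
| 0.7 | 24 | 24/40 = 60% | 28 |

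Unless q = 1, the 40/40 split thus needs unequal allocation among feasible homes.

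**The case against.** The strongest reply is that the article does not exclude covariates from the primary model. It refers to a separate analysis plan, not shown, to be finalised before data lock. Its own analysis section is evidently not exhaustive, since Study design mentions time-related covariates that the analysis section never repeats. This stands as a limit: the absence of a covariate list is not in itself an error. It does not answer the contradiction in the balance promise. Nor does it answer Group 1 vs Group 3, which the article names as a comparison across all randomised households.

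It can also be said that homes are assigned among the arms available to them, so infeasible homes are simply balanced over two arms. That is probably the intention, but the promise as worded says four.

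Some stronger readings are tempting but unsupported:
- A reader might infer that four factors alone leave fewer homes per stratum than arms. With binary factors the average is 5.0. The shortfall needs the feasibility layer or a three-level factor.
- A reader might infer that stratification achieves nothing. It still reduces imbalance in every setting tried, and the true variance falls even without adjustment.
- A reader might infer that standard errors which ignore the strata inflate false positives. The error runs the other way.
- A reader might infer that leakage, size and exhaust fans should be dropped as strata. Dropping a factor returns its imbalance to about 0.16. Moreover, leakage enters the ERV airflow calculation, as does floor area. With levels unstated, this is a trade-off and not a fault.

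**Conclusion.** The point holds in this form: the stated primary model does not name the variables that govern allocation, and the balance promise cannot be met as worded for infeasible homes.

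The precision loss is moderate and conservative. The range of 5-21% rests on an assumed 10-40% of variance explained, binary factors and blocks of four; counting feasibility as a fifth binary factor gives 3-15%. The thin cells (2.5 homes on average) depend on unstated levels and on full crossing.

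The device comparison matters most. Whatever the number of levels, any feasible share below 1 makes feasibility differ systematically between Group 1 and Group 3. Pre-intervention data remove stable differences in level, but not differences in response or trend between the two kinds of home. Group 1 vs 2 and Group 3 vs 4 are not confounded in this way, because both arms of each pair draw on the same homes.

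**What to change.** **Data management and statistical analysis plan.**
- Include in the primary model air leakage and home size (continuous), exhaust fans, baseline health status and ERV feasibility, each with its interaction with period. The interactions are needed because a main effect of a home-level factor does not adjust a pre-to-post change.
- Restrict Group 1 vs Group 3 to ERV-feasible homes.
- Do not add the pre-period outcome as a covariate while it is also part of the repeated-measures response.

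**Interventions.**
- Make ERV feasibility an explicit randomisation stratum, and promise balance across the arms available in each feasibility layer.
- Optionally, keep the other strata few or minimise within each feasibility layer.

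**Cost.** A few degrees of freedom, and a smaller Group 1 vs Group 3 contrast. If 40/40 is kept with equal active:sham allocation, Group 3 has (80q − 40)/2 feasible homes: 16, 12 and 8 at q = 0.9, 0.8 and 0.7. Against 20 vs 20, the standard error rises by √[(1/20 + 1/n)/(2/20)], a factor of 1.06, 1.15 and 1.32. At q = 0.5 no feasible homes are left for Group 3, so the feasible share should be checked before the split is fixed. Recruitment is ongoing and data collection had not begun at the time of writing. The model wording can be changed until the analysis plan is finalised, but the allocation scheme only until homes are randomised.
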